### Statistical analysis

#### Clinical data analysis

The continuous variables will be described as the mean (standard deviation) or the median. The categorical variables will be described as the percentage. The comparisons between the two groups will be analyzed by independent sample *t* test, Wilcoxon rank-sum, or *χ*^2^ test in demographic, psychological factors and other indicators. The comparison between the acupuncture and sham acupuncture will be analyzed using general liner model. Intention-to-treat analysis (ITT) will be mainly used to evaluate the efficacy of acupuncture. ITT analysis will be performed to analyze all randomized data, and last observation carried forward (LOCF) will be adopted to impute the missing values. Per protocol analysis will be used and per protocol population will include patients who complete at least 10-session acupuncture during each phase and finish 4 fMRI scans. The specific effect of acupuncture will be calculated by subtracting the effect in sham acupuncture from the acupuncture. The nonspecific effect of acupuncture will be calculated by subtracting the pre-acupuncture from the post-acupuncture in sham acupuncture phase. The data will be statistically analyzed by SPSS software.

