## Methods

### Study design

This is a randomized, controlled, crossover clinical trial (Fig. 1). In order to accurately clarify the specific and nonspecific effects of acupuncture, a controlled, crossover trial has been designed to control the interference of individual difference (e.g., demographic characteristics, brain metrics and psychological factors) on the results. This trial has been approved by the ethical committees of Dongzhimen Hospital Affiliated to Beijing University of Chinese Medicine (NO: DZMEC-KY-2017-53-02) and registered in Chinese Clinical Trial Registry (NO: ChiCTR1900025807). The protocol will be reported following Standard Protocol Items: Recommendations for Interventional Trials (SPIRIT) statement (Additional file 1). A total of 60 patients diagnosed with KOA according to American College of Rheumatology clinical criteria will be recruited [25]. After inform consent acquisition, all patients will be randomly assigned to group A and group B based on the ratio of 1:1. The patients in group A will receive acupuncture 3 sessions per week for 4 weeks. After a 2-week washout period, the patients in group A will receive sham acupuncture 3 sessions per week for 4 weeks. The patients in group B will receive the reverse intervention process.

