### Randomization and blinding

Eligible patients will be randomly assigned to one of two groups in a 1:1 ratio. The randomization sequence and grouping will be generated and stored by a specific statistician who will not participate directly in this study using the software SAS 9.3 (SAS Institute, Cary, NC, USA). Acupuncturists cannot be blinded to treatment allocation, and they will not be allowed to discuss with patients the type of intervention. The outcome evaluators, fMRI scanners, statisticians, and all patients will be blinded to group assignment until completion of the study.

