### Clinical outcomes evaluation

The pain-related scales will be used to evaluate the magnitude of acupuncture’s specific and nonspecific effects in treating KOA. The primary outcome will be the change of pain on the Numerical Rating Scale (NRS) after 4 weeks of intervention. And the minimal clinically important improvement (MCII) will be defined as at least 2-point reduction on the NRS, and patients who attain the MCII will be defined as responders [9, 33]. The secondary clinical outcomes will include the change of short-form of the McGill Pain Questionnaire (SF-MPQ) and Western Ontario and McMaster Universities Osteoarthritis Index (WOMAC). The SF-MPQ, which includes sensation and affection of pain [34], will be used to assess the pain quality. The WOMAC consists of three subscales with five-point Likert scale: pain, stiffness, and physical function [35]. Adverse events and blinding assessment during the study will be recorded (Fig. 3).

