#### Mediation analysis

Besides, we will investigate whether the relation between psychological factors and clinical effects of acupuncture are mediated by brain activity by using a method of mediation analysis. In the above analyses, age, gender, and education years will be taken as covariates. The detailed statistical analysis is shown in Fig. 4.

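### The specific and nonspecific effects are defined as unadjusted phase changes, and period, sequence and baseline NRS are not among the named covariates, so a phase difference can distort the patient-level correlations

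*Protocol article*

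**What the plan says.** All references are to the Methods of the protocol article.

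- Clinical outcomes evaluation makes the primary outcome a change score: "The primary outcome will be the change of pain on the Numerical Rating Scale (NRS) after 4 weeks of intervention".
- Clinical data analysis names the model class but no terms: "The comparison between the acupuncture and sham acupuncture will be analyzed using general liner model".
- The same section fixes how the two effects are formed: "The specific effect of acupuncture will be calculated by subtracting the effect in sham acupuncture from the acupuncture" and "The nonspecific effect of acupuncture will be calculated by subtracting the pre-acupuncture from the post-acupuncture in sham acupuncture phase".
- Mediation analysis names the only covariates in the text: "In the above analyses, age, gender, and education years will be taken as covariates". It then refers to Fig. 4 for the detailed analysis; that figure is not shown.
- The sections on neuroimaging, psychological factors and mediation relate clinical improvement to brain and psychological measures by Pearson correlation and mediation.
- Inclusion criteria require NRS of at least 4 in the week before entry. No such threshold is stated for the start of phase II.

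The text does not mention period or sequence as analysis terms, nor baseline NRS as a covariate.

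**The concern.** In a two-period crossover each patient is his or her own control, so fixed characteristics such as age, gender and education already drop out of the acupuncture-sham contrast. Two things do not drop out: a general difference between phases, and random error in the baseline reading of each phase.

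A phase difference is likely here. Patients enter phase I because their pain is high, so regression to the mean makes the phase I change look larger. Phase II starts after a four-week treatment and without that selection.

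Let p be the extra pain reduction seen in phase I whichever treatment is given. The specific effect of a patient who has acupuncture first then carries +p, and that of a patient who has sham first carries −p. The sham-phase change carries p in the sham-first sequence and nothing in the other, that is ±p/2 around its mean. These patient-level values go into the correlation and mediation analyses, on which the second and third objectives depend. Precision of the primary contrast is also at stake, and the Sample size section has no formal calculation that would show a margin for losing it.

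**Working it through.** **Inputs from the article.** Two sequences allocated 1:1, 30 per group, 20% attrition. The article's figure of 30 follows from its 25 subjects as 25 × 1.20 = 30 (25/0.80 = 31.25 would round up to 32). Planned completers: 60 × 0.80 = 48.

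**Assumptions.** The article gives no SD, correlation or phase difference. I take an NRS SD of 2, a pre-post correlation rw within a phase, a correlation rb for any two readings from different phases, and p = 1 or 2 points.

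**1. Mean specific effect.** Bias = p(nA − nB)/(nA + nB), with nA and nB the completers in groups A and B.
- 30:30 or 24:24: bias 0.
- 27:21, p = 1: 6/48 = 0.125 points.
- 28:20, p = 1: 8/48 = 0.17 points.

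In 4,000 simulated trials with 30 per sequence and no treatment effect, the average estimate was 0.00. At p = 2 the unadjusted test rejected in 1.9% of trials, against 5.1% for the model with period and baseline. Omitting period is therefore conservative under balance.

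**2. Correlations with psychological factors.** The SD of a patient's unadjusted specific effect is s = √[4·SD²·(1 − rw)] = √[4·4·0.5] = 2.83 at rw = 0.5. With balanced sequences the ±p multiplies its variance by 1 + p²/s². Sequence is randomized, so it is independent of baseline psychological scores, and the correlation shrinks by 1/√(1 + p²/s²):
- p = 1: 1/√1.125 = 0.94.
- p = 2: 1/√1.5 = 0.82.

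For the nonspecific effect the shift is ±p/2 and the SD of one phase change is √[2·4·0.5] = 2. The factors are 1/√1.0625 = 0.97 and 1/√1.25 = 0.89.

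**3. Brain-symptom correlations.** Suppose the brain and symptom effects are truly unrelated, but both carry a shift of ±d (in units of their own SD) by sequence. The expected correlation is d²/(1 + d²) in absolute value:

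| d in both measures | Correlation from nothing |
|---|---|
| 0.25 | 0.06 |
| 0.5 | 0.20 |
| 1 | 0.50 |

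On the symptom side, p = 1 gives d = 1/2.83 = 0.35 for the specific effect and p = 2 gives 0.71. With an equal brain shift the correlations would be 0.125/1.125 = 0.11 and 0.5/1.5 = 0.33. Balanced allocation does not remove this.

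**4. Precision.**
- Change-score contrast: variance 4·SD²·(1 − rw).
- Contrast of end-of-phase scores adjusted for the baseline difference: 2·SD²·(1 − rb)(1 − b²), with b = (rw − rb)/(1 − rb).
- Since 1 − rw = (1 − rb)(1 − b), the ratio is 2/(1 + b).

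| rb | rw | b | Variance ratio |
|---|---|---|---|
| 0.5 | 0.5 | 0 | 2.00 |
| 0.4 | 0.6 | 0.33 | 1.50 |
| 0.5 | 0.7 | 0.40 | 1.43 |
| 0.5 | 0.8 | 0.60 | 1.25 |

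Two is the ceiling as long as rw is not below rb; the simulation gave 1.94 to 2.08 for equal correlations. With 48 completers:
- rb = rw = 0.5: SE √(8/48) = 0.41 against √(4/48) = 0.29; power for a 1-point difference 69% against 93%.
- rb = 0.4, rw = 0.6: SE √(6.4/48) = 0.37 against √(4.27/48) = 0.30; power 78% against 92%.

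**The case against.** The strongest reply is that the article lists no terms for its general linear model. That model class can hold patient, period, sequence and baseline, a condensed article may leave them to a fuller plan, and Fig. 4 is not shown. This stands. A reader might infer that the primary model omits these terms, but the documents do not establish that; they show only that the terms are not named. It is likewise an inference that the model is fitted to the subtracted changes, because the article states the model and the subtraction in separate sentences.

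Second, the covariate sentence sits under Mediation analysis and may refer only to the correlation and mediation analyses, where patient-level covariates are sensible. That is a fair reading. It does not dispose of the point, because those are the analyses in which sequence matters and is not named.

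Third, a reader might infer that the phase difference biases the average specific effect. Under balanced sequences it does not, and the main analysis is intention-to-treat in all randomized patients. The 28:20 split is only an illustration, and its 0.17 points is small beside the article's 2-point threshold for important improvement.

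Fourth, the change score has a real merit: it removes carry-over that is still present at the phase II baseline, a fair worry given that "After a 2-week washout period, the patients in group A will receive sham acupuncture 3 sessions per week for 4 weeks". Baseline adjustment removes only the fraction b of it, and none when all correlations are equal, which is the case that gives the ratio of 2.0. So it would be wrong to call the unadjusted contrast a loss without benefit.

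Fifth, the attenuation at p = 1 is mild, and a spurious brain-symptom correlation needs both measures to shift between phases. Both statements are correct. The sizes of these shifts are unknown, and that favours adjusting for them in advance.

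**Conclusion.** The point holds in a limited form. The text defines the specific effect as an unadjusted difference of phase changes and the nonspecific effect as a raw sham-phase change, and its named covariates leave out period, sequence and baseline NRS. Followed as written, this lets any phase difference enter each patient's effect with a sign set by sequence.

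The main consequence lies in the mechanism analyses: spurious brain-symptom correlations of about 0.06 to 0.50 for shifts of 0.25 to 1 SD in both measures, and correlations between psychological factors and the specific effect reduced to 0.94 or 0.82 of their size for p = 1 or 2. For the primary contrast the cost is precision, with about 1.25 to 2.0 times the error variance over the correlations shown. A flat statement that the error variance doubles would take the ceiling for the expected value.

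The SD, the correlations and the phase shifts are all assumptions. That a phase difference is likely follows from selecting only phase I entry on NRS; that it is certain does not follow. This is an inexpensive improvement to the specification. It does not show that the average effect is biased or that the analysis is invalid.

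**What to change.** 1. State the terms of the acupuncture-sham comparison: end-of-phase NRS as response; treatment, period and sequence as fixed effects; patient as a random effect; baseline NRS as a covariate. To gain the precision shown, baseline has to be the reading for each phase, entered for example as the patient's mean baseline plus that phase's deviation from it. An entry value that is constant within a patient does not adjust the within-patient contrast.
2. Keep the unadjusted change-score contrast as a sensitivity analysis, because it protects against carry-over present at the phase II baseline.
3. Add sequence and baseline NRS to the covariates listed under Mediation analysis, and use partial correlations or period-adjusted effects in the correlation and mediation analyses. With two periods, sequence fixes the sign of the shift in each patient's effect, so adjusting for sequence removes the ±p.
4. If the full plan or Fig. 4 already contains these terms, one sentence saying so is enough.

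The cost is about two degrees of freedom, a little more analysis work and a change of wording. No new data are needed: the effect definitions already call for a pre-treatment reading in each phase.

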### Sample size

Since this is a pilot study, a formal sample size calculation is not performed [27]. According to fMRI studies, a sample size of 20 subjects are sufficient to detect a significant difference with a type I error of 5%, and about 25 subjects are required when *α* = 0.000002, to achieve a stable statistical power [28–30]. Considering a 20% attrition rate and possible excessive head motions occur in the fMRI scanning, we plan to recruit 30 subjects in each group.

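### LOCF as the only missing-data rule scores an unobserved crossover phase as no response, which attenuates the nonspecific effect and can bias the specific effect either way

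*Protocol article*

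**What the plan says.** The Clinical data analysis section of the protocol article sets the main analysis: "Intention-to-treat analysis (ITT) will be mainly used to evaluate the efficacy of acupuncture". It covers all randomised data, and for gaps "last observation carried forward (LOCF) will be adopted to impute the missing values". No other missing-data method is named.

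The same section defines the two target quantities. For the first, "The specific effect of acupuncture will be calculated by subtracting the effect in sham acupuncture from the acupuncture". The nonspecific effect is obtained by "subtracting the pre-acupuncture from the post-acupuncture in sham acupuncture phase". The Clinical outcomes evaluation section matches this: "The primary outcome will be the change of pain on the Numerical Rating Scale (NRS) after 4 weeks of intervention".

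The Study design section gives group A acupuncture first and then: "After a 2-week washout period, the patients in group A will receive sham acupuncture 3 sessions per week for 4 weeks". For the other sequence: "The patients in group B will receive the reverse intervention process".

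Missing phases are expected. The Sample size section sets recruitment at 30 per group with this allowance: "Considering a 20% attrition rate and possible excessive head motions occur in the fMRI scanning". The Exclusion criteria section also removes patients during the trial for unpermitted analgesics or other treatment, withdrawal of consent, too many missed sessions, or a serious adverse event.

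The only other analysis named is per protocol. It is limited to patients with at least 10 sessions in each phase and all four fMRI scans.

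**The concern.** LOCF fits poorly with an outcome that is a change within a treatment phase. If no NRS score is seen after a phase begins, the carried value serves as both the start and the end of that phase, and the change is zero by construction. For a patient lost between phases, the carried value was also measured under the other treatment, before the washout.

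The two sequences are affected differently. A group A patient lost in phase II is recorded as not responding to sham. A group B patient lost in phase II is recorded as not responding to acupuncture. The first raises the estimated specific effect and the second lowers it.

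The trial's first objective is the size of the specific and nonspecific effects, so the distortion falls on the main quantities. The direction for the specific effect is not reliably conservative. The per-protocol set leaves out the same patients, so it can neither correct nor reveal the problem.

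**Working it through.** **Inputs from the protocol article.** Two sequences, 1:1, 30 patients each; 20% attrition; LOCF under intention to treat; effects defined as above. The article states no figure for the LOCF bias, the effect sizes or the standard deviation.

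**The plan's own figure.** The only related figure is 30 per group. From a base of about 25, 25 × 1.2 = 30, or 25 / 0.8 = 31.25, rounded up to 32. The attrition step is thus reproduced to within two patients. It implies 0.20 × 30 = 6 losses per group. The article does not split these by phase or sequence, and the sample size itself is not in question here.

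**Assumptions.** A = 2.5 and S = 1.8 are the true falls in NRS on acupuncture and sham, so the true specific effect is 0.70 and the true nonspecific effect 1.80. Losses are unrelated to response, and the two sequences are weighted equally.

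**Formulas for phase II losses.** Let pA be the loss in group A (sham phase missing) and pB the loss in group B (acupuncture phase missing), with no NRS score after phase II begins. A lost group A patient contributes A − 0 = A to the specific effect. A lost group B patient contributes 0 − S = −S.

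- Expected specific effect = 0.5 × [(1 − pA)(A − S) + pA × A] + 0.5 × [(1 − pB)(A − S) − pB × S] = (A − S) + 0.5 × (pA × S − pB × A).
- Expected nonspecific effect = S − 0.5 × pA × S. Group B's phase II losses do not enter.

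**Results for phase II losses (pA/pB).**

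| Loss | Bias of specific effect | Specific (true 0.70) | Nonspecific (true 1.80) |
|---|---|---|---|
| 20%/20% | 0.5 × (0.36 − 0.50) = −0.07 | 0.63 (−10%) | 1.62 |
| 10%/30% | 0.5 × (0.18 − 0.75) = −0.285 | 0.415 (−41%) | 1.71 |
| 30%/10% | 0.5 × (0.54 − 0.25) = +0.145 | 0.845 (+21%) | 1.53 |

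**Phase I losses before any follow-up score.** The patient contributes zero to both phases, so at a loss of 20% in both sequences each effect is multiplied by 0.80: specific 0.80 × 0.70 = 0.56, nonspecific 0.80 × 1.80 = 1.44.

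**If interim NRS visits exist.** If half the phase II effect has been seen and is carried, the phase II biases halve. For 20%/20%, the specific effect is 0.70 − 0.035 = 0.665 and the nonspecific effect 1.80 − 0.09 = 1.71.

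**Other assumed effects.** With A = 3 and S = 2 (true specific effect 1.0), the same formula gives 1.20 for 20% phase II loss in group A only, 0.70 in group B only, and 0.90 in both. In a simulation with 30 per sequence, 4,000 runs, and assumed standard deviations of 1.2 between and 1.2 within patients, using observed phases only returned 1.00 and 2.00, to rounding, in every phase II loss pattern tried, with losses at random. With A = S = 2, so no specific effect, 20% loss in one sequence only raised two-sided 5% rejection under LOCF to 14% (group A) and 13% (group B). Equal loss kept it at about 5%.

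**The case against.** The strongest defence is that the article calls this a pilot without a formal sample size calculation, and that the one attrition rate it gives produces a small bias. Equal 20% phase II loss moves the specific effect by 0.07 points toward zero and, with no true effect, leaves the error rate near 5%. The −41% and +21% need 3 against 9 losses, or the reverse, out of 30. If both true rates were 20%, a gap that large would arise by chance in about 7% of trials. Patients are blinded, and nothing in the article predicts such an imbalance. All of this stands and limits the size of the point. It does not remove it, because several of the listed removal reasons could be related to response, so equal loss cannot be assumed.

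A reader might infer more than the article supports:

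- **That sequence sets the direction of bias for both effects.** It does so only for the specific effect under phase II losses. The nonspecific effect is only pulled toward zero, provided sham patients improve.
- **That every lost phase is scored as exactly zero.** This needs no NRS score after the phase begins, and the visit schedule is in Fig. 3, which is not shown.
- **That the carried value usually comes from the other treatment.** This applies to patients lost between phases. Those lost during phase II carry a post-washout or same-phase score. Carrying across phases is itself an inference from intention to treat combined with LOCF, since the article neither states nor excludes it.
- **That no assumption could justify the rule.** One could: no benefit from a phase not received. It is a strong assumption and the article does not argue for it.
- **That the standard errors are wrong by a known amount.** Nothing here quantifies that.

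**Conclusion.** The point holds in this form. Under the stated plan, a phase with no follow-up NRS score is analysed as no response to that treatment. The nonspecific effect is attenuated, by 0.5 × pA × S for phase II losses. The specific effect is biased by 0.5 × (pA × S − pB × A) for phase II losses: upward when mainly sham phases are lost, downward when mainly acupuncture phases are lost, and modestly toward zero under equal loss if A exceeds S. Phase I losses before any follow-up shrink both.

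Under the assumed A = 2.5 and S = 1.8, the specific effect lies between 0.415 and 0.845 against a true 0.70 across the loss patterns shown, and is 0.63 if the planned 20% falls equally in phase II. These sizes rest on assumed effects, assumed placement of losses and no interim visits. That the rule imposes no response, or a partial response if interim scores exist, does not depend on those sizes.

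**What to change.** - Replace LOCF as the primary handling with a linear mixed model on all observed phase data of all randomised patients, with fixed treatment, period and sequence and a random patient effect. It needs no imputation and is valid under missing at random.
- Add multiple imputation or a delta-adjusted analysis as a sensitivity analysis for departures from that assumption.
- If LOCF is kept, label it supportive and do not carry values from one phase into the other.

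The cost is wording in the protocol and the statistical analysis plan, plus a little more analysis. SPSS, the software already named, has a mixed-model procedure. No extra patients, visits or data are needed.

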### Interventions

Each type of acupuncture treatment will include 12 sessions of 30-min duration over 4 weeks (3 sessions per week). The date of each patient’s treatment will be recorded, and the number of treatments received by each patient at intervention phase I and intervention phase II will be counted for monitoring adherence. The licensed acupuncturists with more than 5 years of experience with acupuncture will be trained for a standard intervention procedure before this study. Patients will be given paracetamol sustained-release tablets (Tylenol; Shanghai Johnson Pharmaceutical Co., Ltd.) as a rescue medication when they have excessive pain, and the administration of rescue medication will be recorded in detail.

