### Neuroimaging data evaluation

Many functional systems of the brain are involved in pain modulation, such as descending pain, affective, and cognitive processing systems. Resting state fMRI data will be measured to identify the neurological mechanisms of the specific and nonspecific effects of acupuncture. Functional MRI scanning will be carried out using a Siemens 3.0 Tesla scanner (Skyra, Siemens, Erlangen, Germany) equipped with a standard head coil at the Beijing Hospital of Traditional Chinese Medicine Affiliated to Capital Medical University. During the resting state fMRI acquisition, patients will be in a supine position with their eyes closed and be instructed to remain awake and avoid thinking. The resting state fMRI data will be obtained using a gradient echo planar imaging (EPI) sequence with the following parameters: whole brain, repetition time (TR) = 2000 ms, echo time (TE) = 30 ms, field of view (FOV) = 224 mm × 224 mm, flip angle (FA) = 90°, slice thickness/gap = 3.5/0.6 mm, voxel size =3.5 mm × 3.5 mm × 3.5 mm, axial slices = 32, in-plane resolution = 64 × 64, and 240 volumes. Foam pads will be used to minimize head motion and earplugs will be used to reduce noise interference. The fMRI scans will be performed at baseline and the end of 4-week treatment in each phase (Fig. 3).

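### The only per-protocol set requires four finished fMRI scans, so adherent patients with complete pain data leave the supportive clinical analysis for a missed scan

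*Protocol article*

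**What the plan says.** The protocol article defines a per-protocol set once, in Statistical analysis, Clinical data analysis: the "per protocol population will include patients who complete at least 10-session acupuncture during each phase and finish 4 fMRI scans". Both conditions must be met. Neuroimaging data analysis and Mediation analysis define no set of their own.

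The scan schedule is in Neuroimaging data evaluation: "The fMRI scans will be performed at baseline and the end of 4-week treatment in each phase". The Interventions section plans 12 sessions for each type of treatment, one type per phase.

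The clinical endpoints are in Clinical outcomes evaluation: "The primary outcome will be the change of pain on the Numerical Rating Scale (NRS) after 4 weeks of intervention", with SF-MPQ and WOMAC as secondary clinical outcomes. All are rating scales or questionnaires.

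On the standing of the analyses, Clinical data analysis says: "Intention-to-treat analysis (ITT) will be mainly used to evaluate the efficacy of acupuncture". It continues: "ITT analysis will be performed to analyze all randomized data, and last observation carried forward (LOCF) will be adopted to impute the missing values". The per-protocol analysis is therefore supportive.

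**The concern.** A per-protocol analysis beside intention-to-treat is usually read as the effect in patients who received the treatment as planned. Sessions attended bear on that. Scans do not: they are measurements for the article's second objective, the neurological mechanism, while the clinical scales serve its first objective, the size of the specific and nonspecific effects. Yet a patient with 24 of 24 sessions and every pain rating is removed from the per-protocol analysis of pain if one scan is missed.

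Two things are at stake. The supportive clinical estimate rests on fewer patients than it needs to. It also becomes harder to interpret: if it differs from the intention-to-treat result, the reader cannot tell how much comes from non-adherence and how much from who could be scanned four times. Scanning is a separate burden. It takes place at a different hospital from the one named as the study setting, and the resting-state run alone is 240 volumes at 2 seconds each, or 480 seconds (8 minutes), lying supine.

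**Working it through.** **Step 1: what the rule does.** Two scans per phase (baseline and end of treatment) × two phases = 4 scans, which reproduces the article's figure. Four is thus the whole schedule, with no allowance for a missed scan. The session condition does allow for some absence: at least 10 of 12 in each phase, so up to 2 missed per phase.

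**Step 2: two adherent patients compared.**

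| Patient | Sessions | NRS, SF-MPQ, WOMAC | Scans | Intention-to-treat | Per-protocol |
|---|---|---|---|---|---|
| A | 12 + 12 | complete | 4 of 4 | in | in |
| B | 12 + 12 | complete | 3 of 4 | in | out |

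A and B do not differ in treatment received or in clinical data.

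**Step 3: inputs for the size.** The article gives no missed-scan rate, so the per-scan rate m among adherent patients is assumed to be 2%, 5% or 10%. For a head count, the Sample size section provides planned recruitment: "Considering a 20% attrition rate and possible excessive head motions occur in the fMRI scanning, we plan to recruit 30 subjects in each group". That is 60 in total, and 60 × (1 − 0.20) = 48 after the stated attrition. As an illustration, these 48 are taken as the adherent patients with full clinical data. (The planned 30 per group itself reproduces as 25 × 1.20 = 30. Dividing instead, 25 / 0.80 = 31.25, which rounds up to 32. Nothing here turns on that difference.)

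**Step 4: formulas.** Let q be the share of adherent patients who miss at least one scan.

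- Misses fully clustered, so that a patient who misses one scan misses all: q = m.
- Misses independent across the four scans: q = 1 − (1 − m)^4.
- Standard error relative to a set without the scan condition, if patient-level variance is unchanged: 1/√(1 − q).

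**Step 5: results.**

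| m | q, clustered | Lost of 48 | SE ratio | q, independent | Lost of 48 | SE ratio |
|---|---|---|---|---|---|---|
| 2% | 2% | 1.0 | 1/√0.98 = 1.01 | 1 − 0.98^4 = 7.8% | 3.7 | 1.04 |
| 5% | 5% | 2.4 | 1/√0.95 = 1.03 | 1 − 0.95^4 = 18.5% | 8.9 | 1.11 |
| 10% | 10% | 4.8 | 1/√0.90 = 1.05 | 1 − 0.90^4 = 34.4% | 16.5 | 1.23 |

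If misses tend to fall in the same patients, as is plausible, the loss lies between the two halves of the table.

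**The case against.** The strongest reply is that little depends on this set. Intention-to-treat on all randomized patients is the main efficacy analysis, and the trial calls itself a pilot. That stands, and it limits the point to a supportive analysis.

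A second reply is that a joint completer set is sensible in a mechanism study, because the correlation and mediation analyses need symptom and brain data in the same patients, and the scans are scheduled for everyone. The need is real, but it does not justify the rule. Those analyses can use their own scan-complete set without shrinking the clinical one.

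A third reply is that independent misses overstate the loss. This also stands, and so the range starts from full clustering. The exclusion of claustrophobia and other MRI contraindications should also keep the rate down.

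Three stronger readings are tempting, but the article does not support them:

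- **That the rule biases acupuncture against sham.** Patients in more pain might be less willing to be scanned, but the article has no data on this. In a crossover, excluding a patient removes both phases, so selection on a stable trait mainly changes who is represented. Bias between the treatments would need scan loss that depends on response to one of them. The article neither shows this nor rules it out.
- **That the rule also lets scans ruined by motion into the imaging analysis.** The wording asks for finished scans, not usable ones. But the article does not say that this set is the only imaging filter. Data management and monitoring has a technician check quality after each scan, and Sample size allows for head motion.
- **That a comparison with intention-to-treat would say nothing about adherence.** The session condition remains in the rule, so the comparison is mixed rather than empty.

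**Conclusion.** The point holds as a defect in a supportive analysis. The stated rule removes adherent patients from the per-protocol analysis of NRS, SF-MPQ and WOMAC for lacking data that those outcomes do not use. The primary conclusion is unaffected.

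The cost in precision depends on a rate that the article does not give. Over the assumed per-scan rates of 2% to 10%, it runs from negligible (2% of adherent patients, standard error up about 1%) to appreciable (34.4%, standard error up about 23%). The upper figure needs both the highest assumed rate and independent misses. The head counts further assume 48 adherent patients. The mixing of adherence with scan availability needs no particular rate: it arises whenever an otherwise eligible patient misses a scan. Whether it brings bias, and in which direction, cannot be determined from the article.

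**What to change.** Replace the single definition with two, before unblinding:

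- **Clinical per-protocol set:** at least 10 sessions in each phase, as now, with no scan condition. Use it for NRS, SF-MPQ and WOMAC.
- **Imaging set:** all four scans done and passing the quality check. Use it for the ALFF, ReHo and functional connectivity analyses, the brain-symptom correlations and the mediation analysis.

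Report the number of patients in each set and in both.

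This takes a sentence or two in the analysis section and needs no new data, visits or change to treatment. The downside is two sets to track and report, and clinical and imaging results that may rest on slightly different patients. The overlap count lets the reader judge how much that matters.
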